### Secondary analysis

The secondary analysis will test differences in the mean score of all continuous secondary outcomes at the primary, secondary and final endpoints and will be performed in the same way as the primary analysis. Nominal outcomes will be analysed by the chi-squared test or in cases with less than five expected counts for any observation, Fishers exact test will be used.

At baseline descriptive statistics will be presented. At each endpoint, mean scores, standard deviations, between-groups mean (with corresponding 95% confidence intervals) and p-values will be reported (see extended data item 4: analysis outline for primary and secondary analysis
^23^).

### Additional analyses

As the age of the participants may vary and affect the results of the study, we will undertake an exploratory, age-related subgroup analysis. Definition of analysis population relating to protocol non-adherence

All analyses will follow the intention-to-treat (ITT) principle (analysed as randomized). Additionally, per protocol (PP) analysis will be done for the primary outcome. All patients with an exercise adherence of at least 80 % will be considered adherent to the rehabilitation strategy and included in the PP analysis. All patients in the no rehabilitation group will be included in the PP analysis. Missing values in both ITT and PP analysis will be imputed by multiple imputation. Imputation models will be based on all other available variables in the data.

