### Adherence and concomitant care

During the first consultation, the importance of following the study guidelines and adhering to the allocated group will be highlighted. Exercise adherence will be recorded as a percentage of completed exercises (based on adherence to the prescribed exercise frequency and repetitions) during the first follow up (after the 6-week intervention) for both the home-based telerehabilitation and home-based rehabilitation groups. Exercise adherence will be taken into consideration when performing the per-protocol analysis (please see the statistical methods section).

All enrolled patients will be encouraged to contact the principal investigator directly, if experiencing problems related to their recent surgery or to their allocated group intervention. The principal investigator will then fill out a standardized form at these calls. Patients can use pain-relief products as needed, prescribed by their physician after their surgery. To avoid study-contamination, patients will be asked to adhere to the allocated rehabilitation intervention and not to seek alternative health-care services specific to their hip- or knee arthroplasty during the course of the study. Patients will be advised to contact their general practitioner or the principal investigator as needed.

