*Analgesics.* The use of analgesics will be recorded at baseline and at all follow-up assessments, using a nominal scale (yes/no) regarding the daily consumption of opioids, non-steroid-anti inflammatorily drug (NSAID) and paracetamol. If the patient is not aware of his or her use of analgesics, a medical record will be obtained to assess the use of analgesics. 

*Walking assistant devices.* The type and number (e.g. one or two elbow crutches) will be recorded at baseline and at all follow-up assessments. The need for walking assistant devices will be assessed by the number of walking assistant devices the patient uses during normal activities of daily living.

*Patient satisfaction.* Patient satisfaction will be assessed at the end of the 6-week intervention, where patients will be asked to answer four questions to indicate their level of satisfaction. The answers will be based on a 4-Likert ordinal scale with the categories: very satisfied (100 points), somewhat satisfied (75 points), somewhat dissatisfied (50 points), and very dissatisfied (25 points). The score is the unweighted mean of the combined scores. The four questions are: “How satisfied are you with the results of your surgery and rehabilitation?”, “How satisfied are you with your surgery and rehabilitation for improving your pain?”, “How satisfied are you with the results of your surgery and rehabilitation for improving your ability to do home or yard work?” and “How satisfied are you with the results of surgery and rehabilitation for improving your ability to do recreational activities?”. The questions are modified from the self-administered patient satisfaction scale for primary hip and knee arthroplasty
^39^ and have in its original form proven to be a valid and reliable outcome measurement for patient satisfaction following THA and TKA
^39^.

*Exercise adherence.* Exercise adherence will be measured as a percentage (0–100), where 0 % indicates total non-adherence and 100 % indicates total adherence to the exercise prescription. Exercise adherence in the home-based telerehabilitation and home-based rehabilitation group will be measured as a self-reported outcome, where patients will be asked: “What percentage of the prescribed 42 exercise sessions (one exercise session per day for 6 weeks; corresponding to 100 %) have you completed the past 6 weeks?”

*Adverse events.* Adverse event during enrolment of the trial will be recorded, regardless of the relation to the trial.

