### Primary analysis

The primary analysis will evaluate the mean difference at 6 weeks follow-up between physical rehabilitation (home-based telerehabilitation and home-based rehabilitation) and no physical rehabilitation. This will be assessed by independent two-sample t-tests if normality assumptions are acceptable, otherwise the Wilcoxon sum rank-test will be used. The same tests will also be used to compare the individual physical rehabilitations to no physical rehabilitation.

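### The per-protocol set selects rehabilitation patients on adherence after randomisation but keeps every control, so it is no longer a randomised comparison and probably favours rehabilitation

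*Protocol article*

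**What the plan says.** Under Additional analyses, the protocol article makes intention-to-treat the rule for all analyses and then adds: "Additionally, per protocol (PP) analysis will be done for the primary outcome". Membership of the PP set is fixed differently by arm. For the two exercise arms: "All patients with an exercise adherence of at least 80 % will be considered adherent to the rehabilitation strategy and included in the PP analysis". For the control arm: "All patients in the no rehabilitation group will be included in the PP analysis".

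The only tests named are unadjusted. Under Primary analysis: "This will be assessed by independent two-sample t-tests if normality assumptions are acceptable, otherwise the Wilcoxon sum rank-test will be used".

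Adherence is described in two places. Adherence and concomitant care defines it as a "percentage of completed exercises (based on adherence to the prescribed exercise frequency and repetitions", and says that it feeds the PP analysis. Elaborated description of outcome measures defines it by one self-report question in the two exercise arms: "What percentage of the prescribed 42 exercise sessions" has the patient completed.

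Two other sections bear on who falls below 80%. Criteria for modifying the allocated intervention tells exercise patients with severe symptoms to lower intensity, then volume, then stop until pain has eased; only the exercise arms get these instructions. Criteria for discontinuing the allocated intervention ends participation after postoperative complications in any arm, but retains those patients for follow-up.

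**The concern.** Adherence is known only after randomisation and may depend on how recovery is going. A rehabilitation patient with persisting pain or a complication tends to exercise less, can fall below 80% and then leaves the PP set. A control patient with the same course always stays. The two sides are no longer comparable at baseline in expectation, and an unadjusted t-test or Wilcoxon test does nothing to restore comparability.

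The analysis concerns the primary outcome, and the likely direction is that of the trial's hypothesis. If a null intention-to-treat result appeared beside a favourable PP result, the pair could be taken to mean that rehabilitation works for those who do it, when selection alone could produce the pattern.

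A smaller, separate matter is that the 80% cut is not uniquely defined. A patient who completes all 42 sessions at reduced volume is 100% adherent by the session question, but could fail a definition that counts repetitions.

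**Working it through.** **Inputs from the article (Sample size; Statistical methods).** SD 20; clinically important difference 10 points, which is also the superiority criterion; 100 rehabilitation patients and 50 controls evaluable.

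**The plan's own figures.** With a standardised difference of 10/20 = 0.5, a two-sample t-test at one-sided 5% needs 50.15 per group for 80% power and gives power 0.890 for 100 versus 50. Both match the stated 50 and 0.89. With 10% loss, 50/0.9 = 55.6, so 56. A two-sided 5% test does not reproduce them (about 64 per group; power 0.82). The article does not state the sidedness and gives no figure for the PP set.

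**Assumptions (the article gives neither value).** The adherent share p, and the correlation r between adherence and the recovery that the patient would have had anyway. Exercise has no effect.

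**Size of the shift.** If adherence and outcome are bivariate normal and only the top share p is kept, the mean of those kept moves by

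bias = SD × r × φ(z)/p, with z = Φ⁻¹(1 − p).

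For p = 0.6: z = −0.253, φ(z) = 0.386, φ(z)/p = 0.644. The bias is 20 × 0.644 × r = 12.88r.

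**Consequence for the test.** About 60 adherers against 50 controls gives SE = 20 × √(1/60 + 1/50) = 3.83. A two-sided 5% test has 2.5% nominal error on the favourable side.

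| r | Bias (points) | Bias/SE | Significant in favour of rehabilitation (simulated) | PP contrast ≥ 10 points (simulated) |
|---|---|---|---|---|
| 0.2 | +2.6 | 0.67 | about 9.5% | about 3% |
| 0.3 | +3.9 | 1.01 | about 17% | about 5% |
| 0.4 | +5.2 | 1.34 | about 28% | about 10% |

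Hand check at r = 0.3: P(Z > 1.96 − 1.01) = 17%, and P(Z > (10 − 3.86)/3.83) = P(Z > 1.60) = 5.5%. Without selection, the chance of reaching 10 points would be P(Z > 10/3.83) = 0.5%.

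**Range.** For p from 0.5 to 0.9 and r from 0.1 to 0.4, the bias runs from +0.4 (p = 0.9, r = 0.1) to +6.4 (p = 0.5, r = 0.4). Favourable significant results run from about 3% to 37.5%. At p = 0.8 and r = 0.2 to 0.4, the bias is +1.4 to +2.8 points, and 10 points is reached in only about 1% to 2% of trials. With negative r the sign reverses: p = 0.7, r = −0.2 gives −2.0 points.

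**Same result without the normal model.** With no effect, bias = (1 − p) × (mean of adherers − mean of non-adherers). If adherers score 10 points better, the bias is 0.4 × 10 = +4 at p = 0.6 and 0.2 × 10 = +2 at p = 0.8.

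**The case against.** The strongest reply is that the PP analysis carries little weight. The article states: "All analyses will follow the intention-to-treat (ITT) principle (analysed as randomized"; the PP analysis is additional, and no section bases a claim on it. A reader might infer that the trial's main conclusion is biased. The documents do not support that, and this limits the severity.

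A reader might also infer that the PP set is certainly biased towards rehabilitation. That too goes beyond the documents. Fast recoverers may stop exercising because they feel no need. The pain rule is graded and its stop is temporary. Lower intensity need not reduce the session count, and 80% of 42 is 33.6, so a patient must miss at least 9 sessions to be dropped. Controls who obtain rehabilitation, and are still kept, would pull the contrast towards zero if rehabilitation works. The article tries to limit this: patients are asked not to seek other care for the joint, and the institution is the only one of its kind on the island. The direction is therefore an expectation.

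Third, significance is not the article's criterion for a claim. It asks for a contrast of at least 10 points, and every bias computed above is below that. The rates for reaching 10 points (about 3%, 5% and 10%) are the relevant ones for a claim and are lower than those for p < 0.05.

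Finally, controls have no prescribed exercise to adhere to, so any adherence-based set is asymmetric to some degree. That is true, but it is a reason to restrict what the set may support; it does not make the comparison valid.

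**Conclusion.** The point holds in a limited form. As written, the PP rule selects on a post-randomisation variable in the exercise arms only, and breaks the randomised comparison for the primary outcome. The article's own links from pain and complications to reduced exercise make a bias towards rehabilitation the more likely direction, without establishing it.

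With no true effect, SD 20 and 60% adherent, correlations of 0.2 to 0.4 give a spurious gain of about a quarter to a half of the 10-point criterion. The adherent share and the correlation are assumptions. High adherence makes the bias small, and a negative correlation reverses it. The two adherence definitions add ambiguity about who is in the set, but are a lesser issue. This should be corrected, and it does not threaten the intention-to-treat result.

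**What to change.** 1. Use one adherence definition for the 80% cut. Reconcile the wording based on frequency and repetitions with the self-reported share of 42 sessions, which is already asked in both exercise arms.
2. Label the 80% PP result descriptive and open to selection bias, and state that it cannot support a superiority claim.
3. For the effect of adhering, report a complier-type (instrumental-variable) estimate: all patients as randomised, allocation as instrument, adherence as exposure set to 0 in controls, no covariates (as in the primary analysis), and the same imputations. In this simple form it is the intention-to-treat difference divided by mean adherence in the rehabilitation arms. A zero intention-to-treat difference therefore stays zero, and selection cannot create a benefit.

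The cost is analysis wording; no new data are needed. State the estimate's downsides beside it: a wider confidence interval; reliance on self-reported adherence; the assumption that allocation acts only through exercise, which is doubtful with unblinded patients and a patient-reported outcome; and the assumption that controls had no prescribed exercise. If the third step is not wanted, the first two are the minimum.

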### Data monitoring and auditing

No data monitoring committee will be composed, as the interventions pose little or no known risk for the participating patients. Likewise, no auditing procedures are expected to take place.

### Sample size

A clinically important difference of 10 points on the HOOS/KOOS subscale function in daily living (ADL)
^36,
45^ is used as our superiority margin, with an expected standard deviation of 20 points, a power of 0.80 and a significance level of 0.05 resulting in a sample size of 50 patients in each group. With 10% loss to follow up
^46^ this results in 56 patients in each group. This calculation will be used for each comparison of individual physical rehabilitations to no physical rehabilitation; therefore, 56 patients are needed for each of the three groups resulting in 168 patients included in total (3 groups of 56 patients). Comparison of any physical rehabilitation to no physical rehabilitation is done under the same clinically important difference and expected standard deviation as the individual comparisons. With a sample size of 100 (patients receiving one of the two physical rehabilitation strategies) and 50 (patients receiving no physical rehabilitation) the expected power is 0.89.

We expect a relatively low inclusion rate of 50%, since one of the interventions includes “no physical rehabilitation”, compared to standard rehabilitation. Furthermore, based on the expected patient flow at our trial sites and the need to conduct the trial within a realistic timeframe, we do not initially intend to stratify THA and TKA for subgroup analysis. There will not be any specific strategies for increasing participant enrolment related to this trial.

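### The stated sample size (50 per group, power 0.80) and pooled power (0.89) hold only for a one-sided 5% test that the protocol never declares; with two-sided tests the powers are about 0.70 and 0.82

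*Protocol article*

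**What the plan says.** The Sample size section gives a complete calculation. It assumes a clinically important difference of 10 points on the HOOS/KOOS ADL subscale, "with an expected standard deviation of 20 points", and "a power of 0.80 and a significance level of 0.05 resulting in a sample size of 50 patients in each group". Allowing for 10% loss to follow-up, this becomes 56 per group and 168 in total. The section ties the calculation to the individual strategies: "This calculation will be used for each comparison of individual physical rehabilitations to no physical rehabilitation". For both rehabilitation arms combined (100 patients) against no rehabilitation (50 patients), under the same difference and SD, it says "the expected power is 0.89".

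The Primary analysis section plans independent two-sample t-tests, or the Wilcoxon rank-sum test if normality is not acceptable, and does not say whether they are one- or two-sided. The Secondary analysis section says that, at each endpoint, "between-groups mean (with corresponding 95% confidence intervals) and p-values will be reported". The opening of Statistical methods words the hypothesis directionally (rehabilitation better than none) but sets no tail for the test.

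**The concern.** A significance level of 0.05 with no qualifier is normally read as two-sided, and the 95% intervals support that reading. Under it, 50 per group is too few for 80% power at a standardised difference of 0.5.

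Two things are at stake. First, interpretation of a null result. The Pragmatism section says the municipality wants an estimate of the effectiveness of telerehabilitation before it invests, and the 0.80 figure is attached to exactly that kind of individual comparison. A non-significant result would be read as coming from a comparison with a 20% chance of missing the assumed effect, when under two-sided testing the chance is about 30%. Second, undeclared sidedness leaves the error rate open. A two-sided p-value between 0.05 and 0.10 in favour of rehabilitation is significant at one-sided 5% and not at two-sided 5%, so the choice could be made after the data are seen.

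**Working it through.** **Inputs** (all from the Sample size section): difference 10; SD 20; alpha 0.05; power 0.80; 50 per group, or 100 vs 50 pooled; loss 10%. Standardised difference d = 10/20 = 0.5.

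**Formulas** (normal approximation)
- Patients per group: n = 2(z_alpha + z_power)² / d²
- Power: Φ(10/SE − z_alpha), with SE = 20·√(1/n₁ + 1/n₂)
- z_power = 0.842; z_alpha = 1.645 one-sided, 1.960 two-sided

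**1. Reproducing the protocol's figures: one-sided 5%**
- n = 2(1.645 + 0.842)²/0.25 ≈ 49.5, so 50 per group
- 50/0.9 = 55.6, so 56 per group and 3 × 56 = 168
- 50 vs 50: SE = 20·√(2/50) = 4.00; Φ(2.500 − 1.645) = Φ(0.855) ≈ 0.804
- 100 vs 50: SE = 20·√(0.03) = 3.464; Φ(2.887 − 1.645) = Φ(1.242) ≈ 0.893

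Every stated figure is recovered.

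**2. The same calculation at two-sided 5%**
- n = 2(1.960 + 0.842)²/0.25 ≈ 62.8, so 63 per group
- 50 vs 50: Φ(2.500 − 1.960) = Φ(0.540) ≈ 0.705
- 100 vs 50: Φ(2.887 − 1.960) = Φ(0.927) ≈ 0.823

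Neither stated figure is recovered.

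**3. Check with the noncentral t, which matches the planned t-test**

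| Quantity | Stated | One-sided 5% | Two-sided 5% |
|---|---|---|---|
| n per group for 80% power | 50 | 51 (unrounded 50.2) | 64 (unrounded 63.8) |
| Power, 50 vs 50 | 0.80 | 0.799 | 0.697 |
| Power, 100 vs 50 | 0.89 | 0.890 | 0.818 |
| Power, 56 vs 56 (no loss) | – | 0.838 | 0.746 |
| Power, 112 vs 56 (no loss) | – | 0.919 | 0.859 |

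The choice of formula moves n by one patient per group and the power by less than 0.01. It cannot account for 50 against 63 or 64. Two separately stated figures (50 per group and 0.89) both fit one-sided 5%, and neither fits two-sided 5%.

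**4. What 80% two-sided power would have required**
- Normal approximation: 63/0.9 = 70 per group, 210 in total
- Noncentral t: 64/0.9 = 71.1, so 72 per group, 216 in total
- Planned and recruited: 168

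**The case against.** The strongest reply is that the calculation contains no slip. Taken as one-sided, all its figures agree with one another, and the hypothesis and the superiority claim are worded in one direction, which fits a one-sided test. If that was the intention, the stated powers are right for the planned analysis. The article also refers to an analysis outline in its extended data, which is not shown and may state the sidedness. The 95% interval is a reporting convention, described under Secondary analysis, and is not itself a decision rule.

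Some of this stands. The arithmetic is sound under a one-sided reading, so the shortfall depends on the test being two-sided, and what can be said of sidedness is confined to this article. It does not remove the problem. A directional hypothesis does not fix the tail of the test; superiority trials are routinely tested two-sided. The interval statement applies at each endpoint, and the Analysis outline section makes the 6-week assessment the primary endpoint, so it covers the primary comparison. A one-sided 5% test corresponds to a 90% interval, so a one-sided sample size and 95% intervals imply different error rates. The article publishes the calculation in full with a bare 0.05, so a reader cannot be expected to look elsewhere to learn that it is one-sided.

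A further reply is that the protocol claims superiority when the observed contrast reaches 10 points, and that power to reject zero difference does not describe this rule. That is true, but it is a separate matter and does not support the stated 0.80 or 0.89, which are themselves powers to reject zero difference.

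**Conclusion.** The concern holds. The 50 per group with power 0.80 and the pooled power of 0.89 are correct only for a one-sided 5% test, which the article does not declare and which its 95% intervals contradict. At two-sided 5% the powers are 0.70 (50 vs 50) and 0.82 (100 vs 50), or 0.75 and 0.86 if nobody is lost to follow-up, so neither stated power is reached in either case.

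These figures rest on the protocol's own difference of 10 and SD of 20, the t-test, and no adjustment for multiple comparisons. The 10% inflation from 50 to 56 is correct and is not in question. This should be corrected before the primary results are analysed, because it affects the stated power of all the primary comparisons and the threshold for calling them significant.

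**What to change.** Recruitment closed at 168 (Dissemination policy section, study status), so no design change is proposed.

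- In Primary analysis, state that all primary tests are two-sided at 0.05, consistent with the 95% intervals.
- In Sample size, replace the power statements with, for example: *With 50 patients per group, a difference of 10 points and an SD of 20, the power at two-sided alpha 0.05 is 0.70 for each individual rehabilitation strategy against no rehabilitation, and 0.82 for the pooled comparison (100 vs 50).*
- If a one-sided 5% test was truly intended, say so explicitly in both sections, keep 0.80 and 0.89, and report the matching 90% interval. If the extended-data outline already declares it, cite that.

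The cost is wording only. Under the two-sided option, the stated power becomes less favourable.

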## Ethics and dissemination

### Ethical approval and consent

This trial obtained approvals from the Ethics Committee of the Capital Region Denmark
^28^ and the Danish Data Protection Agency
^29^ and was registered in a public trial registry before the first participant was enrolled. Written consent from each trial participant will be obtained during the first consultation at our outpatient facility by an experienced physiotherapist.

